#### Secondary outcomes measures

The number of symptomatic sore throat episodes within the first 12 monthsThe number of days of incapacity for work/inability to go to the kindergarten/school and sore throat related limitation in daily routine cumulated at 6, 12, 18, and 24 monthsTonsil and Adenoid Health Status Instrument (TAHSI) and the Tonsillitis Outcome Inventory-14 (TOI-14) prior and after surgery at 6, 12, 18, and 24 months [9–11]Quality of life assessed by Short Form-12 (SF-12) Questionnaire prior to surgery and after surgery at 6, 12, 18, and 24 months [12]Cumulative number of days using analgesics because of sore throat within 24 monthsCumulative number of days using antibiotics because of sore throat within 24 monthsSafety analyses: morbidity and mortality after surgery, primary/secondary bleedings within 24 months; intraoperative and postoperative complicationsRevision tonsil surgery within 24 months

### Participant timeline {13}

Table 1 gives an overview of the participant timeline. Baseline characteristics of the subjects will be compiled at informed consent. Subjects will be randomly divided into an intervention arm and a control arm with the aid of a computer-based randomization module in a 1:1 ratio. Stratified randomization is accomplished using age group (< 18 years, ≥ 18 years and study center. All tonsillotomies and tonsillectomies will be carried out under general anesthesia. Surgery will be performed by all grades of doctors, from residents to specialists. Which from the allowed techniques is chosen depends on the surgeon’s experience and preference. If a tonsillotomy was performed, the study center has to decide, if the patient is treated as a day care case or if a therapy as an in-patient is indicated. All tonsillectomy patients are treated as in-patients. After surgery, all patients will be kept in the ward for at least 3–5 days. All patients receive standard pain management depending on the study center choice. After discharge, the participants will primarily be contacted by a mobile application called the TOTO app designed to run on mobile devices like mobile phones, tablet, or watch. Alternatively, the participant can enter the data via a link on the internet. Participants/parents who do not have a needed electronic device will receive a paper-based diary. We assume that about 75% of the participants are able to use the app. Using the app, the participants will be contacted weekly with a push-function of the app and asked if they had sore throat in the previous 7 days. If the participant did not experience sore throat in the last 7 days, the questioning ends. If the participant experienced sore throat in the last 7 days, the app automatically opens a sore throat questionnaire with ten questions on pain intensity and sore throat-related limitations. Furthermore, each study center will contact their participants for a telephone interview after 6, 12, 18, and 24 months. At these four times points, the participants should answer again the TAHSI, the TOI-14, and the SF-12 questionnaire.

**Table 1 Tab1:** Standard Protocol Items of the TOTO trial: Recommendations for Interventional Trials (SPIRIT) table of the trial schedule for enrolment, interventions, and follow-up/assessments

			Study period							
	Clinic visit	Admission	Post-allocation							Close-out
Timepoints	Registry	Scheduled	0	POD1-5	Weekly to POM 24	POM 6	POM 12	POM 18	POM 24	POM 24

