## Methods: Participants, interventions, and outcomes

### Study setting {9}

Patients will be recruited from twenty hospitals (in-patient and out-patient) across Germany. An up-to-date list of study sites will be published online on the TOTO homepage (https://toto-studie.hno.org/). Only study centers with at least 10 tonsil surgeries and a principal investigator with GCP certificate are eligible.

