**Assessments**										
**Demographic data**	X	X								
**Additional Adenoidectomy**		X								
**TAHSI**	X					X	X	X	X	
**TOI-14**	X					X	X	X	X	
**SF-12**	X					X	X	X	X	
**Weekly App alert**					X					
**If sore throat: sore throat questionnaire**					X					
**Complications, AE**			X	X	X					X
**Participation sign-off**										X

*AE* adverse event, *NRS* numeric rating scale, *POD* postoperative day, *POM* postoperative month, *SF* Short Form Health Survey, *TAHSI* Tonsil and Adenoid Health Status Instrument, *TOI* Tonsillectomy Outcome Inventory

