## Assignment of interventions: blinding

### Who will be blinded {17a}

Participants and involved otolaryngologists will not be blinded. Blinding is not possible because it will be obvious for the participant/parents and involved otolaryngologists when looking into the mouth, if a tonsillotomy or a tonsillectomy was performed. Furthermore, postoperative pain is normally much lower after tonsillotomy. The involved biostatistician will be blinded until database lock. The assessment of the primary endpoint and secondary endpoints is following a strict evaluation algorithm. The blinded statistician and an independent otolaryngologist make up the endpoint committee. If an individual evaluation of an endpoint remains unclear, the endpoint committee will discuss the case. All confirmatory analyses will be comprehensively specified in the predefined statistical analysis plan to avoid any reporting bias.

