### Adverse event reporting and harms {22}

An adverse event (AE) will be defined as any untoward medical occurrence in a participant without regard to the possibility of a causal relationship. AEs will be collected after the participant has provided consent and enrolled in the study. If a participant experiences an AE after the informed consent document is signed (entry) but the participant has not started to receive study intervention, the event will be reported as not related to the intervention. All AEs occurring after the entry into the study and until discharge from the study will be recorded. After discharge from the hospital, i.e., during the follow-up phase at home, the participants are asked to report AE at least during the weekly app consultation. An AE that meets the criteria for a serious adverse event (SAE) between study enrollment and discharge will be reported to the local Ethics committee and the sponsor as an SAE. If the tonsil surgery is discontinued as a result of an AE, study personnel will document the circumstances and data leading to the discontinuation of treatment. A SAE for this study is any untoward medical occurrence that is believed by the investigators to be causally related to study intervention and results in any of the following: life-threatening condition (that is, immediate risk of death); severe or permanent disability, prolonged hospitalization, or a significant hazard as determined by the DMC. SAE occurring after a participant is discontinued from the study will NOT be reported unless the investigators feel that the event may have been caused by the study drug or a protocol procedure. Investigators will determine the relatedness of an event to study intervention based on a temporal relationship to the study intervention, as well as whether the event is unexpected or unexplained given the subject’s clinical course, previous medical conditions, and concomitant medications.

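### The ward-stay rule contradicts the day-care option for tonsillotomy; if day care is used, early complications may be observed differently by arm and centre

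*Protocol article*

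**What the plan says.** Three consecutive sentences in the protocol article, Participant timeline {13}, set the care setting:

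- After tonsillotomy, "the study center has to decide, if the patient is treated as a day care case"; the alternative it names is in-patient care.
- For the control arm the setting is fixed: "All tonsillectomy patients are treated as in-patients".
- The length of stay is then given without regard to arm or setting: "After surgery, all patients will be kept in the ward for at least 3–5 days".

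Study setting {9} adds: "Patients will be recruited from twenty hospitals (in-patient and out-patient) across Germany".

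On safety data, Table 1 has a row "Complications, AE" marked at time 0, on postoperative days 1 to 5, weekly to month 24 and at close-out, with no distinction by arm or care setting. Adverse event reporting and harms {22} says that after hospital discharge "the participants are asked to report AE at least during the weekly app consultation". Outcomes {12} lists bleedings and intraoperative and postoperative complications among the secondary outcomes. On blinding, section {17a} states: "Participants and involved otolaryngologists will not be blinded".

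**The concern.** A site cannot follow all three sentences for a tonsillotomy patient whom it treats as a day case. Because the lower limit of the stay is itself a range, two sites that keep everyone in could also apply different minimum stays.

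The statistical interest lies in what follows if day care is used. Day care is open to one arm only, at the centre's discretion. In the first postoperative days, clinical staff would then be observing the tonsillectomy patients, while some tonsillotomy patients would be reporting on themselves from home. Early minor bleeding or other minor complications could be recorded less completely after tonsillotomy, and more so at centres that use day care often. In an open-label trial, an arm-dependent method of observation can produce an apparent safety difference where none exists. The abstract's discussion makes reduced morbidity, together with at least equal effectiveness, the condition under which tonsillotomy would save costs. The safety comparison therefore carries weight even though it is secondary.

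**Working it through.** **Step 1: is there a contradiction?** Read literally, the ward sentence covers all patients, so it includes any day-case tonsillotomy patient. A day case has no stay of several days, so the sentences cannot both hold. The mention of out-patient care in Study setting {9} sets no stay rule, but it suggests that the day-care option is intended and is not a slip.

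**Step 2: what follows under each reading?**

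| Reading | Stay rule consistent? | First postoperative days |
|---|---|---|
| Ward sentence governs for everyone | Only if the day-care option is removed | Both arms on the ward; setting does not differ by arm |
| Day-care sentence governs | Only if the ward sentence is changed | Tonsillectomy on the ward; tonsillotomy on the ward or at home, by centre |
| Ward sentence meant for in-patients only | Yes, but the text does not say so | As in the row above |

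Every reading needs a correction to the text. Two of the three allow early observation to differ by arm and centre.

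**Step 3: how are early events collected from a patient at home?** Table 1 schedules the assessment on postoperative days 1 to 5 for all. The only route described after discharge is participant self-report, with weekly as the minimum frequency. The weekly contact in Participant timeline {13} is described as a sore-throat question that ends if the answer is no. Data management {19} lists documentation of adverse events among the data that centres transfer to the eCRF. Care setting and discharge date are not in that list.

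**Step 4: how many patients could be involved?** The plan's own sample size reproduces. With a negative binomial rate ratio on the log scale, n per arm = (1.960 + 0.842)² × 2 × (1/7.56 + 0.44) / (ln 0.8)² = 180.4, rounded up to 181. Then 181/0.8 = 226.25, rounded up to 227 per arm and 454 in total. At most 227 tonsillotomy patients could therefore be day cases. The article gives no expected share, and the point changes none of these figures.

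**Step 5: direction and mechanism, with assumed figures.** Let p be a true early minor-complication rate common to both arms, f the share of tonsillotomies done as day cases, and d_w and d_h the detection probabilities on the ward and at home. With no true difference, the apparent advantage of tonsillotomy is p × f × (d_w − d_h). None of these four quantities is in the document. Assuming p = 10% and d_w = 95%:

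| Assumed d_h | f = 1 | f = 0.5 |
|---|---|---|
| 60% | 0.10 × 1 × 0.35 = 3.5 points (6.0% vs 9.5%) | 0.10 × 0.5 × 0.35 = 1.75 points (7.75% vs 9.5%) |
| 85% | 0.10 × 1 × 0.10 = 1.0 point | 0.10 × 0.5 × 0.10 = 0.5 points |
| 95% | 0 | 0 |

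The apparent advantage is also 0 if f = 0. The table shows direction and what the bias depends on. It is not an estimate for this trial.

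**The case against.** The strongest reply accepts that the sentences conflict and disputes the consequence.

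- *The ward sentence may govern, or may be loose prose meant for in-patients.* If it governs for everyone, setting does not differ by arm. This stands, and it is why the concern about detection is conditional. The in-patients-only reading removes the contradiction but leaves the possible difference in observation.
- *Table 1 already provides a common early assessment, and weekly reporting is a floor.* This also stands, and it may reduce the gap. How that assessment is completed at home could be in a full protocol or CRF manual that is not shown, so its absence from the article is not itself the fault. The fault is the contradictory stay rule, which leaves open whether such patients exist.
- *The outcomes are secondary and the events minor.* Agreed. A bleed that needs readmission would probably be found in either setting.

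A reader might infer more than the document supports. One inference is that early complications will in fact be detected differently by arm; that holds only if day care is used and the scheduled early assessment is carried out differently at home. Another is that the safety result is biased by some 3.5 points; that figure rests wholly on assumed rates and on every tonsillotomy being a day case. A third is that the non-inferiority conclusion is at risk; nothing in these sentences changes the primary sore-throat analysis or its sample size.

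**Conclusion.** The contradiction in Participant timeline {13} is real and does not depend on any assumption: the day-care option and the ward stay for all patients cannot both be followed, and the minimum stay is not a single value. The possible bias is conditional. It needs the day-care option to be used, and it needs the assessment on postoperative days 1 to 5 to be less complete at home than on the ward. If both hold, it would tend to favour tonsillotomy on early, mainly minor, complications and would vary by centre. Its size cannot be derived from the document. It is worth correcting because the safety comparison is open-label and the remedy is small. No view is taken on which care setting or length of stay is right.

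**What to change.** 1. Reconcile the three sentences in Participant timeline {13}, consistently with Study setting {9}, into one rule that every site can follow. The choice of stay rule is the sponsor's.
2. Whatever the rule, state that the complication and bleeding assessment already scheduled in Table 1 for postoperative days 1 to 5 uses the same question set, on the same postoperative day, for every patient in both arms, on the ward or at home. The existing app or diary can carry it. Because diaries are collected only every six months, a paper entry should be dated when it is completed.
3. Record care setting and discharge date in the eCRF, so that early events can be described by setting.

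The cost is a wording change, one extra early prompt per patient and two eCRF fields. No further visits or patients are needed.

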**Enrollment**										
**Eligibility screen**	X									
**Informed consent**	X									
**Baseline information**	X									
**Allocation**		X								
**Interventions**										
**Tonsillotomy**			X							
**Tonsillectomy**			X							
**Assessments**										
**Demographic data**	X	X								
**Additional Adenoidectomy**		X								
**TAHSI**	X					X	X	X	X	
**TOI-14**	X					X	X	X	X	
**SF-12**	X					X	X	X	X	
**Weekly App alert**					X					
**If sore throat: sore throat questionnaire**					X					
**Complications, AE**			X	X	X					X
**Participation sign-off**										X

*AE* adverse event, *NRS* numeric rating scale, *POD* postoperative day, *POM* postoperative month, *SF* Short Form Health Survey, *TAHSI* Tonsil and Adenoid Health Status Instrument, *TOI* Tonsillectomy Outcome Inventory

### Sample size {14}

Non-inferiority of a tonsillotomy compared to tonsillectomy is given when the threshold of the lower limit of the 95% confidence interval for a difference in the number of days of sore throat is above 80%. Assuming a rate of 7.56 days within 24 months in both groups, a dispersion parameter of 0.44, and a significance level of 2.5%, a negative binomial regression analysis would detect a significant difference of the quotient of the rates compared to a non-inferiority limit of 0.8 with an 80% power, if 181 participants were treated in both arms. Assuming a loss of follow-up data of 20%, 454 patients have to be randomized.

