### Objectives {7}

The primary study objective is to compare the frequency of sore throat episodes within 24 months after tonsillotomy versus tonsillectomy in children and adults treated for recurrent acute tonsillitis. We hypothesize that the frequency of sore throat episodes is not higher after tonsillotomy compared to tonsillectomy. Secondary objectives are the frequency of sore throat episodes within the first 12 months after surgery, the days of incapacity of work/out of school, tonsil-specific quality of life, need for treatment with antibiotics, and need for treatment with analgesics within 24 months after surgery. Furthermore, mortality and morbidity (primary and secondary bleedings and other intraoperative and postoperative complications will be evaluated as well as the need for re-surgery within 24 months.

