## Statistical methods

### Statistical methods for primary and secondary outcomes {20a}

Continuous variables will be presented as means and standard deviation or median and interquartile range (IQR) if not normally distributed. Categorical data will be presented as a number with a percentage. The primary analysis is performed on the per-protocol (PP) set and sensitivity analyses in the intention-to-treat (ITT) and full analysis population are also planned.

Differences between the observed risks of events (for primary outcomes of sore throat days) between both groups will be calculated along with their 95% confidence intervals by negative binomial regression. The non-inferiority of the tonsillotomy compared to the tonsillectomy in the number of symptomatic sore throat days within 24 months is evaluated by means of negative binomial regression with the stratification factors as a covariate and the non-inferiority margin of 0.8 to a one-sided significance level of 2.5%. In secondary outcome, the number of symptomatic sore throat days within 12 months after surgery is evaluated using the negative binomial regression with the stratification factors as a covariate and the non-inferiority margin of 0.8. Other parameters like the PROM results are evaluated using analyses of covariance (ANCOVA), with the stratification variables and baseline observations as covariates. Number of days with the inability to work/attend kindergarten/school after 24 months are evaluated by negative binomial regression with stratification variables as covariates. A one-sided significance level of 2.5% will be considered statistically significant (or 5% when testing two-sided). All confirmatory analyses are fully specified in a statistical analysis plan (SAP), which is written before database lock and before unblinding the trial statistician, in order to avoid reporting bias. The results are published independently of the statistical results in order to avoid publication bias.

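### The primary non-inferiority rule does not say which arm is the numerator of the rate quotient; on the usual reading, a lower limit above 0.8 is the wrong bound for a harmful count

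*Protocol article*

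**What the plan says.** The decision rule stands in Sample size {14}. It opens with "Non-inferiority of a tonsillotomy compared to tonsillectomy is given when" and sets as condition that "the lower limit of the 95% confidence interval for a difference in the number of days of sore throat is above 80"%. The next sentence bases the calculation on the "quotient of the rates compared to a non-inferiority limit of 0.8".

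Statistical methods for primary and secondary outcomes {20a} announces "Differences between the observed risks of events (for primary outcomes of sore throat days") with 95% confidence intervals from negative binomial regression. It then tests non-inferiority with "the non-inferiority margin of 0.8 to a one-sided significance level of 2.5"%. The same 0.8 is carried over to the 12-month secondary outcome.

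The direction of benefit is in Objectives {7}: "We hypothesize that the frequency of sore throat episodes is not higher after tonsillotomy compared to tonsillectomy".

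No section names the numerator of the quotient, and none gives an upper limit.

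**The concern.** Fewer sore throats are better, so the error to guard against is a rate that is too high after tonsillotomy. For a ratio with tonsillotomy on top, only an upper confidence limit guards against it. A lower limit above 0.8 on that ratio shows merely that tonsillotomy is not more than 20% better.

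The only order of comparison in the text is tonsillotomy relative to tonsillectomy, with tonsillectomy as the control arm (Intervention description {11a}). An analyst would ordinarily code the model that way. The rule works only with the opposite orientation, which the reader has to supply.

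The scale is also loosely described: a difference, a quotient of rates and differences between risks, whereas negative binomial regression yields a rate ratio. No single sentence gives measure, numerator and bound together.

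This is the trial's primary decision rule, and the Discussion expects the result to inform a national decision on tonsillotomy.

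**Working it through.** **Inputs**, all from Sample size {14}: mean 7.56 in both arms, dispersion k = 0.44, one-sided 2.5%, 80% power, limit 0.8, 181 per arm, 20% loss, 454 in total.

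**Step 1: reproduce the sample size.** On the log rate-ratio scale, with true ratio 1,

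n per arm = (1.960 + 0.842)² × (1/7.56 + 1/7.56 + 2 × 0.44) / (ln 0.8)² = 180.4, rounded up to 181.

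181 / 0.8 = 226.25, rounded up to 227 per arm, so 454 in total. The plan's figures are reproduced, and power at 181 per arm is 80.1%.

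**Step 2: can the sample size reveal the orientation?** No. |ln 0.8| = ln 1.25 = 0.2231, so a lower limit of 0.8 and an upper limit of 1.25 both give 180.4.

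**Step 3: chance of declaring non-inferiority under each orientation.** Let r be the true ratio tonsillotomy/tonsillectomy.

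- SE(r) = √[(1/7.56 + 1/(7.56 r) + 0.88) / 181]; at r = 1 this is 0.0795.
- Rule A, quotient tonsillotomy/tonsillectomy, lower limit above 0.8: P = Φ[(ln r − ln 0.8)/SE − 1.96].
- Rule B, quotient tonsillectomy/tonsillotomy, lower limit above 0.8 (the same as tonsillotomy/tonsillectomy upper limit below 1.25): P = Φ[(ln 1.25 − ln r)/SE − 1.96].

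Example for rule A at r = 1.25: SE = 0.0786, and Φ(0.4463/0.0786 − 1.96) = Φ(3.72), about 99.99%.

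| True ratio r | Mean days after tonsillotomy | Rule A passes | Rule B passes |
|---|---|---|---|
| 0.7 | 5.29 | 0.02% | about 100% |
| 0.8 | 6.05 | 2.5% | 99.98% |
| 0.9 | 6.80 | 31.3% | 98.4% |
| 1.0 | 7.56 | 80.1% | 80.1% |
| 1.1 | 8.32 | 98.1% | about 37% |
| 1.25 | 9.45 | 99.99% | 2.5% |
| 1.5 | 11.34 | about 100% | about 0% |
| 2.0 | 15.12 | about 100% | about 0% |

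The two rules agree only at equality. Rule B has the intended properties: 80% power at equality and 2.5% error at the margin. Rule A reverses them.

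**Step 4: the same in terms of the observed estimate.** With SE 0.0795 the confidence limits lie a factor exp(1.96 × 0.0795) = 1.169 from the estimate. Under rule A any observed tonsillotomy/tonsillectomy ratio above 0.8 × 1.169 = 0.935 passes. Under rule B any ratio below 1.25 / 1.169 = 1.070 passes.

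**The case against.** The strongest reply is that the text does not fix rule A. It speaks of a quotient without naming the numerator, and with tonsillectomy on top the printed words are a correct test. The objective, that "the frequency of sore throat episodes is not higher after tonsillotomy compared to tonsillectomy", makes sense of a lower limit above 0.8 only in that orientation, so the intention can be recovered. The analysis plan, which is not shown, is to specify all confirmatory analyses before database lock and may settle the contrast. The word *difference* is loose, but a limit of 80% followed by a quotient can only mean a ratio. Nothing numerical in the design is wrong.

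Most of this stands. A reader might infer that, as written, tonsillotomy passes however much worse it is. The documents do not support that: it depends on an orientation they never state. Nor may 1.25 be quoted as the protocol's margin; it is the reciprocal of 0.8. A reader might also take 80% to mean a tolerated excess of 20%, but no such figure appears.

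The reply does not remove the defect. The article states a decision rule rather than leaving it to the analysis plan, and the only order of comparison it gives leads to the wrong bound. That the intention can be guessed from the objective is a reason to write it down.

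**Conclusion.** The primary rule is incompletely specified, and on its usual reading it points the wrong way. Under that reading tonsillotomy would be declared non-inferior with about 99.99% probability at a true ratio of 1.25 (9.45 against 7.56 days, 1.89 more over 24 months) and with 2.5% probability at 0.8, where it is better. Under the inverse quotient the rule is valid, with 2.5% error at the implied limit of 1.25.

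The probabilities are conditional on the orientation and rest on the plan's mean, dispersion and number per arm, with a Wald interval on the log scale. The finding is that the orientation is missing, not that the trial is bound to reach a wrong conclusion. Because it concerns the primary decision, it must be corrected before the analysis.

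**What to change.** In Sample size {14} and Statistical methods {20a}, state once and identically:

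- the effect measure is the rate ratio for the primary count from the negative binomial model;
- which arm is the numerator;
- the bound: tonsillectomy/tonsillotomy with the lower limit of the two-sided 95% confidence interval above 0.80, equivalently tonsillotomy/tonsillectomy with the upper limit below 1.25. The sponsor should confirm that 1.25, implied by 1/0.8, is the intended margin.

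Replace the wording about a difference and about differences between risks with *rate ratio*, and apply the same definition to the 12-month outcome. The sentence should also name the count: Objectives {7} and Outcomes {12} speak of episodes, whereas these two sections speak of days.

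The cost is one sentence in each section and a matching line in the analysis plan. If 1/0.8 is confirmed, 181 per arm and 454 in total stand unchanged.
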